#### Secondary outcomes

2.9.2

ADAS-cog, K-BDI, BAQ, fNIRS, DMTS, BPM, and HRV will be the secondary outcomes. Endpoints will include the change in ADAS-cog, K-BDI, BAQ, DMTS scores, and fNIRS values from visit 1 to visit 25; HRV values from visit 1 to visit 5, 9, 13, 21, and 25; and BMP values from visit 1 to visit 25. As primary outcome, we will use the covariance analysis model that includes each group as a fixed factor, ADAS-cog, K-BDI, BAQ, DMTS scores and HRV, BPM, and fNIRS values as dependent variables, and differences in demographic characteristics as covariates. A paired *t* test or Wilcoxon signed-rank test will be performed on the same participant on the secondary outcome before and after treatment in each group.

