#### NF training method

2.5.2

The intervention group will perform the NF sensorimotor rhythm (SMR) training protocol, whereas the control group will have EEG measured for the 30 minutes of acupuncture treatment.

The ProComp 2 Neurofeedback system (Promp Infiniti 8 channel system, Model NO. BA500, Thought Technology Ltd., Quebec, Canada) will be used in this trial. After cleaning the electrode location with an abrasive conductive gel (Nuprep, Weaver and company, CO) and filling the electrode cups with conductive gel (ten 20 conductive paste, Weaver and Company, CO), an electrode will be placed at the subject's central scalp area according to the international 10/20 system. A reference and ground electrode will be placed on the left and right earlobes, respectively. A 3-electrode location input impedance will be maintained under 5 kΩ.^[26]^

The training session will consist of a 6-minute baseline trial and a 30-minute NF training trial, divided into 6 segments. To determine threshold values, each subject will be measured at baseline SMR wave (12–15 Hz, low beta waves) for 3 minutes with eyes closed and 3 minutes with eyes open. NF training, which is designed to increase threshold SMR values, will be performed 6 times for 5 minutes with 20 to 30 seconds of rest between each trial. BPM and HRV values will also be collected in each trial. The threshold value at each trial is newly set according to the subject's feedback.

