### Sample size

2.6

Considering a 10% dropout rate, we conclude that a total of 44 patients is needed to measure the feasibility of combined NF-acupuncture treatment (effect size 0.8, 0.05 significance level in 2-tailed test, 69% power).^[27]^ If the dropout rate is higher than expected, even after deliberation, the number of participants can be adjusted.

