### Statistical analysis

2.8

All categorical data will be presented as frequencies or percentiles, and will be analyzed by the Pearson chi-squared test or Fisher exact test. All numeric data will be presented as mean, standard deviation, and will be analyzed by Student independent sample *t* test or Wilcoxon rank-sum test to determine normality. Efficacy analysis will be conducted according to the primary full analysis set principle and secondarily by the per protocol principle. All statistical analyses will be based on a two-tailed test and statistically, the significance is set at *P* < .05. The analysis tool will be SAS Version 9.4 (SAS Institute. Inc., Cary, NC). Missing values will be imputed by the last-observation-carried-forward method.

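### HRV is defined as five changes per participant but is given the single-change covariance model, with no visit 1 value as covariate, no visit structure and no named key visit

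*Protocol article*

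**What the plan says.** Section 2.9.2 (Secondary outcomes) sets the HRV endpoint as the change from visit 1 to each of five later visits: "HRV values from visit 1 to visit 5, 9, 13, 21, and 25; and BMP values from visit 1 to visit 25". ADAS-cog, K-BDI, BAQ, DMTS and fNIRS each have one change, from visit 1 to visit 25.

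The same section gives all secondary outcomes the approach of the primary outcome: "we will use the covariance analysis model that includes each group as a fixed factor", with "differences in demographic characteristics as covariates". Section 2.9.1 applies that model to MoCA-K, which has one change per participant. Section 2.9.2 adds within-group tests: "A paired *t* test or Wilcoxon signed-rank test will be performed on the same participant on the secondary outcome before and after treatment in each" of the two arms.

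Section 2.8 sets one level throughout: "All statistical analyses will be based on a two-tailed test and statistically, the significance is set at *P* < .05". It also fills missing values by carrying the last observation forward.

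Three other places bear on HRV and breathing rate (BPM):

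- Section 2.5.2 says of the training session that "BPM and HRV values will also be collected in each trial", so a session yields several values per participant.
- Section 2.2 describes HRV as measured during neurofeedback training, while Table 1 schedules HRV at visit 25, where no treatment is given.
- For BPM, section 2.9.2 gives visit 1 to visit 25, the abstract's wording can be read as covering all visits, and Table 1 shows the breath signal at visits 1 to 24 only.

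**The concern.** The endpoint and the model do not match. A model for one change per participant is assigned to an endpoint with five, and the article does not say how one is applied to the other. Two analyses fit the text. One is a separate covariance model at each visit. The other is a single model holding all five changes. They have different error properties, and neither is tied to a visit that would count as the HRV result.

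At stake is how an HRV finding could be read. With five visits tested at P < .05 and none singled out, whichever visit looks best can be presented as the effect of neurofeedback on HRV. In addition, the visit 1 value is collected but not used as a covariate, which gives up precision in a trial of about 40 completers. Carrying values forward would also let one early reading from a participant who drops out stand in for several later visits.

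**Working it through.** **Inputs.** 44 participants, 22 per arm, 10% dropout (abstract; section 2.6): 44 × 0.9 = 39.6, about 20 per arm. Five HRV changes per participant (section 2.9.2). Two-sided 0.05 (section 2.8). The correlation between HRV changes is not given, so it is assumed and varied.

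**The plan's own figure.** Section 2.6 states "effect size 0.8, 0.05 significance level in 2-tailed test, 69% power". For a two-sample t test with 20 per arm, the noncentrality is 0.8 / √(1/20 + 1/20) = 2.53 on 38 degrees of freedom, which gives power 69.3%. The stated 69% is reproduced, so the trial was sized for a comparison with one value per participant.

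**Correlation of the five changes.** If the raw HRV values have equal variance σ² and equal correlation ρ between visits, each change from visit 1 has variance 2σ²(1 − ρ). Two changes share the visit 1 value and have covariance σ²(ρ − ρ − ρ + 1) = σ²(1 − ρ). Their correlation is 0.5 whatever ρ is. With correlation that decays over time (AR(1) raw values), the mean correlation of the changes was 0.54 to 0.62. A central value of 0.5 is therefore reasonable, but it is an assumption.

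**Reading 1: one model per visit.** Each participant contributes one row to each model, so no participant or visit term is needed. In simulation without a group effect (20,000 trials, 20 per arm), each visit's test rejected in about 5%. Five independent tests would give at least one P < .05 with probability 1 − 0.95⁵ = 22.6%; correlation lowers this.

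**Reading 2: all five changes in one model as independent rows.** Let r be the correlation between changes. The design effect is 1 + 4r and the actual level is 2 × [1 − Φ(1.96/√(1 + 4r))]. At r = 0.5 this is 2 × [1 − Φ(1.96/√3)] = 25.8%.

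| Correlation of changes | Per visit: each test | Per visit: at least one of five | Pooled: formula | Pooled: simulated | One test on participant mean |
|---|---|---|---|---|---|
| 0.3 | about 5% | 20.7% | 18.6% | 18.5% | 5.1% |
| 0.5 | about 5% | 18.6% | 25.8% | 26.8% | 4.8% |
| 0.7 | about 5% | 15.6% | 31.5% | 32.7% | 5.0% |

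With 22 per arm the any-of-five rates were 21.0%, 18.5% and 14.6%. Under the AR(1) variants (20 per arm) the any-of-five rate was 16% to 18% and the pooled rate 28% to 30%.

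**Value of the visit 1 covariate.** With equal variances and correlation ρ between visit 1 and a later visit, the residual variance is σ²(1 − ρ²) when the visit 1 value is a covariate, against 2σ²(1 − ρ) for a plain change. The ratio is (1 + ρ)/2, that is 0.65, 0.75 and 0.85 at ρ = 0.3, 0.5 and 0.7. Adjustment thus removes 15% to 35% of the variance at no cost in data.

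**The case against.** The strongest defence is that nothing in the article says the five changes are pooled. Most outcomes under the same model sentence have one change each, so the natural reading is one covariance model per named visit. That is a valid analysis, and every such test holds its level. What remains is unadjusted testing of a secondary outcome over five prespecified visits in a trial labelled a pilot, which is common. An article may also leave covariance structure, key visit and multiplicity to the full protocol (version 1.3) or to an analysis plan.

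Most of this stands. A reader might infer that the HRV comparison has a false-positive rate of 18% to 26% because the model lacks participant and visit terms. The documents do not support that. The two figures are different quantities: about 26% is the error of one pooled test, and about 18% is the chance of any positive among five separate tests. Missing participant or visit terms do not cause the second, and adding them would not by itself lower it; naming one contrast does. The pooled figure also needs an analysis that the article never states.

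The defence does not remove the mismatch in what the article does state. It fixes an endpoint with five changes and a model for one, lists only demographic covariates, and identifies no visit as the HRV result. A later document would have to qualify that text, not merely fill it in.

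**Conclusion.** The point holds as a modest one. Section 2.9.2 leaves the HRV analysis undetermined between per-visit and joint analysis, omits the visit 1 value as covariate and names no key visit.

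Read per visit, each HRV test is valid at about 5%, with about an 18.5% chance of at least one nominally significant visit when the changes correlate 0.5 (about 21% to 15% for correlations 0.3 to 0.7). Only under pooling of rows as independent would a single test reach about 26% (about 19% to 32% over the same range). These figures assume equally correlated changes, about 20 completers per arm and no true effect; the correlations are not from the documents.

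MoCA-K and the secondary outcomes with a single change are not affected by this mismatch. BPM may be, depending on which visits are analysed. The matter is worth correcting because a better analysis is available at very little cost, not because the plan states an invalid test.

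**What to change.** In section 2.9.2, give HRV its own analysis sentence:

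- For each HRV parameter, fit one repeated-measures mixed model with group, visit (5, 9, 13, 21, 25), group-by-visit and the visit 1 value, and a within-participant covariance: unstructured, with compound symmetry and Kenward-Roger degrees of freedom as the prespecified fallback if it does not converge. Use observed data, not carried-forward values.
- Name one group contrast in advance as the HRV comparison. Visit 25 is a candidate, once it is confirmed that HRV is measured there under conditions comparable with the treatment visits; section 2.2 and Table 1 need to be reconciled on this.
- Report the other visits as estimates with 95% intervals.
- Reduce each session to one HRV value per participant by a rule that works identically in both arms. Section 2.5.2 describes separate training trials only for the intervention arm, while controls have a continuous 30-minute recording.
- Apply the same model to BPM if more than one post-baseline visit is analysed, and reconcile the abstract, section 2.9.2 and Table 1 on which visits those are.

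The cost is a paragraph of wording and one SAS PROC MIXED call per parameter, with no new data, visits or participants. The downside is small. Covariance parameters must be estimated from about 40 participants (5 × 6 / 2 = 15 if unstructured, hence the fallback), and the earlier visits lose their stand-alone P values.

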#### Safety assessment and adverse events report

2.9.3

Evaluating changes in laboratory test results from screening to visit 25, checking of vital signs, and interviews about adverse events at each visit will be performed for safety assessment and adverse event reports.

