**Methods and design::**

This study is a randomized, assessor-blind, pilot trial. It is designed in accordance with the Standards for Reporting Interventions in Controlled Trials of Acupuncture. A total of 44 MND participants who meet the inclusion and exclusion criteria will be enrolled, and each will be randomly assigned to 1 of 2 groups of 22 subjects. Each subject will visit 24 times over 12 weeks and receive either acupuncture or NF-acupuncture combined treatment. At visit 25 (week 13), a follow-up evaluation will be performed, and then the investigator will analyze the results. The primary outcome is defined by the Korean version of the Montreal Cognitive Assessment score from screening to visit 25. The secondary outcome includes the following: change in Alzheimer Disease Assessment Scale–Cognitive, the Korean version of the Beck Depression Inventory, Body Awareness Questionnaire, delayed matching to sample task scores, and functional near-infrared spectroscopy values, from visit 1 to visit 25; heart rate variability values from visit 1 to visit 5, visit 9, visit 13, visit 21, visit 25; breath per minute values from visit 1 to visit 1 to 25.

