### Study procedure

2.4

All consenting participants will be subjected to the measurement of vital signs (blood pressure, pulse rate, body temperature), demographic information survey, medical history (past, present, family), physical examination, laboratory tests, and electrocardiogram tests. Eligible participants who meet the inclusion and exclusion criteria will receive a schedule of visits (screening).

At visit 1, the investigator will check the subject's vital signs and test ADAS-cog, K-BDI, BAQ, DMTS (response and accuracy), and fNIRS (Oxy-Hb, deOxy-Hb). The control group will receive acupuncture treatment for 30 minutes, while measuring a simple EEG with NF, and the intervention group will receive acupuncture for a minute while performing the NF training protocol (5 times for 5 minutes, 30–60 seconds of rest between each trial). In the meantime, the investigator will check the subject's BPM and HRV. The investigator will check the subject's adverse reactions and concomitant medications and inform them that cigarettes and caffeine must be avoided 2 hours before the test, as they affect the HRV. From visits 2 to 24, both groups will be treated in the same manner as visit 1, and BPM HRV will be checked in the meantime. The investigator will check the subject's adverse reactions and concomitant medications and inform them in the same manner as on visit 1. At visit 24, the investigator will check the subject's vital signs and test ADAS-cog, K-BDI, BAQ, DMTS (response and accuracy), and fNIRS (Oxy-Hb, deOxy-Hb). Additional visits may be performed at any time if deemed necessary by the investigator's judgment, or following the subject's request. In the event of an unexpected visit, the following tests will be performed: vital signs, checking adverse reactions or concomitant drugs, and laboratory tests. In principle, administration of concomitant drugs will be prohibited during the trial, and when combination therapy may occur, it will be decided whether or not to drop out or exclude at the discretion of the principle investigator (PI). A detailed outline of the schedules is shown in Table 1.

**Table 1 T1:** Schedule of trial visits.

	Study period				
Visit	Screening	1	2 to 24	25	UV
Informed consent	О				
Eligibility screen	О				
Demographic information	О				
Drug history	О				
Medical history	О				
Vital signs	О	О	О	О	О
Laboratory test	О				Δ
EKG	О				Δ
MoCA-K	О			О	
ADAS-cog		О		О	
K-BDI		О		О	
BAQ		О		О	
HRV		О	О	О	

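### The safety section analyses laboratory change from screening to visit 25, but no laboratory test is scheduled after screening, so this one of three safety components cannot be computed from planned data

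*Protocol article*

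**What the plan says.** Section 2.9.3 of the protocol article bases safety on three things: "Evaluating changes in laboratory test results from screening to visit 25", vital signs, and adverse-event interviews at each visit.

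Table 1 ("Schedule of trial visits") has five columns: screening, visit 1, visits 2 to 24, visit 25 and unexpected visit (UV). The row "Laboratory test" has a circle at screening, a triangle at UV, and nothing in the other three columns.

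The text of section 2.4 puts laboratory tests in two places. One is the screening work-up: "medical history (past, present, family), physical examination, laboratory tests, and electrocardiogram tests". The other is the unexpected visit: "In the event of an unexpected visit, the following tests will be performed: vital signs, checking adverse reactions or concomitant drugs, and laboratory tests". The end-of-treatment list reads "At visit 24, the investigator will check the subject's vital signs and test ADAS-cog, K-BDI, BAQ, DMTS (response and accuracy), and fNIRS" and names no laboratory test.

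Section 2.8 gives one missing-data rule: "Missing values will be imputed by the last-observation-carried-forward method". It does not say which variables the rule covers.

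**The concern.** A change score needs two measurements. Section 2.9.3 promises one whose second measurement the schedule does not provide. If the site follows Table 1, the value is never taken, and no later analysis document can supply it.

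Section 2.1 makes efficacy and safety together the main objective, and laboratory change is the first safety item listed. At stake is whether the trial can say anything about laboratory safety by arm. The only later values would come from unexpected visits, which happen when the investigator thinks one is needed or the participant asks. Those participants are a selected group, measured at irregular times. Because section 2.7 states that participants cannot be blinded, the tendency to ask for a visit could also differ between arms.

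**Working it through.** There is no calculated figure in the plan to reproduce here. The sample-size figures have no bearing on the point, beyond the total of 44 from the abstract ("each will be randomly assigned to 1 of 2 groups of 22 subjects", so 2 × 22 = 44). The check is a comparison of passages.

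**Step 1: is the blank cell real?** The laboratory row was set against other rows of Table 1.

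| Row | Screening | 1 | 2 to 24 | 25 | UV |
|---|---|---|---|---|---|
| Vital signs | O | O | O | O | O |
| MoCA-K | O | – | – | O | – |
| Laboratory test | O | – | – | – | Δ |
| EKG | O | – | – | – | Δ |

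Vital signs fill all five columns, and MoCA-K sits at screening and visit 25 as section 2.9.1 requires. The visit 25 column therefore came through intact, and the blank in the laboratory row is not a fault of text extraction.

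**Step 2: what does the schedule supply?** Scheduled laboratory values per participant: one at screening, none at visits 1 to 25. Participants with a scheduled value after screening: 0 of 44. The change, visit 25 value minus screening value, lacks its first term for everyone.

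**Step 3: does another reading rescue it?** Section 2.9.3 could mean the period from screening to visit 25 rather than two time points. That does not help, because no laboratory test is scheduled anywhere in that period after screening.

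**Step 4: can unexpected-visit tests stand in?** They occur only in some participants and at arbitrary times, so they do not give a visit 25 value. The triangle is not explained in the table notes, and section 2.4 says without qualification that the tests will be done at such visits. On either reading they are not scheduled.

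**Step 5: what would LOCF do, if it were applied here?** This step is conditional. Let k be the number of participants with an unexpected-visit laboratory test. The documents give no expected k, so the values below are assumptions. Each of the other 44 − k participants has only the screening value; carried to visit 25, it gives screening minus screening = 0. For the k others, the unexpected-visit value would be carried forward.

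| Assumed k | Changes forced to zero | Share of 44 |
|---|---|---|
| 0 | 44 | 100% |
| 2 | 42 | 95.5% |
| 4 | 40 | 90.9% |
| 8 | 36 | 81.8% |

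**The case against.** The strongest reply is that the conflict is small: one clause against one blank cell, in a pilot whose other safety data are well provided for. Table 1 schedules vital signs at every visit and adverse-effect checks at visits 1, 2 to 24, 25 and UV, and section 2.9.4 sets out how events are described. This stands. A reader might infer that safety as a whole cannot be assessed; the documents do not support that, since two of the three components are scheduled.

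Second, it would be wrong to say that laboratory tests are taken only at screening. Table 1 and section 2.4 both provide for them at unexpected visits. Screening is the only scheduled occasion.

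Third, a reader might infer that the plan will report zero laboratory change in both arms and take it as evidence of safety. The documents do not say so. The LOCF sentence stands in the paragraph that defines the efficacy analysis sets; the safety sets are described separately in section 2.9.4 without any imputation; and a test never scheduled is not clearly a missing value. The more ordinary outcome is that no laboratory change would be reported. The LOCF point therefore holds only as a conditional remark.

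Fourth, the silence of section 2.4 is weak support. That section does not describe visit 25, and its visit 24 list also leaves out MoCA-K, which Table 1 does place at visit 25. The contradiction rests mainly on Table 1 against section 2.9.3.

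None of this removes the contradiction. Nor is it a detail that an article may leave to a fuller document: the article states the analysis and also prints a schedule that cannot feed it.

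**Conclusion.** The point holds in a limited form. Section 2.9.3 and Table 1 disagree on whether a visit 25 laboratory test exists. On the schedule as printed, 0 of 44 participants have a planned laboratory value after screening, so one of three stated safety components cannot be computed from planned data. This is an internal inconsistency. It does not touch the primary outcome, the randomization, the sample size or the efficacy analysis.

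The conclusion assumes that Table 1 is what the site follows. If the full protocol does schedule the test, the article's table is the error and the correction lies there. The zero-change figures in the working depend on two further assumptions, that LOCF is extended to laboratory data and how many participants have an unexpected-visit test; the main conclusion needs neither.

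**What to change.** Reconcile section 2.9.3 with Table 1 and section 2.4, in one of two ways.

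1. If the laboratory-change analysis stays, show the visit 25 laboratory test in Table 1 and section 2.4, for both arms. The cost is one test per participant (at most 44) at a visit that already takes place. It has to be settled before participants reach visit 25, because values not taken then cannot be recovered.
2. If the test is not intended, remove the laboratory-change analysis from section 2.9.3. State that laboratory data serve screening and event-driven checks only, list any unexpected-visit results descriptively, and draw no between-arm conclusion on laboratory safety. The cost is text alone.

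Under the first route, add a sentence to section 2.8 that LOCF does not apply to laboratory values and that the number of participants with an observed pair is reported by arm. Under the second, the same sentence is only a safeguard. If either change counts as an important protocol modification, section 2.12 requires IRB approval.
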